## Abstract

**Background:**

Endometriosis affects 190 million women and those assigned female at birth worldwide. For some, it is associated with debilitating chronic pelvic pain. Diagnosis of endometriosis is often achieved through diagnostic laparoscopy. However, when isolated superficial peritoneal endometriosis (SPE), the most common endometriosis subtype, is identified during laparoscopy, limited evidence exists to support the common decision to surgically remove it via excision or ablation. Improved understanding of the impact of surgical removal of isolated SPE for the management of chronic pelvic pain in women is required. Here, we describe our protocol for a multi-centre trial to determine the effectiveness of surgical removal of isolated SPE for the management of endometriosis-associated pain.

**Methods:**

We plan to undertake a multi-centre participant-blind parallel-group randomised controlled clinical and cost-effectiveness trial with internal pilot. We plan to randomise 400 participants from up to 70 National Health Service Hospitals in the UK. Participants with chronic pelvic pain awaiting diagnostic laparoscopy for suspected endometriosis will be consented by the clinical research team. If isolated SPE is identified at laparoscopy, and deep or ovarian endometriosis is not seen, participants will be randomised intraoperatively (1:1) to surgical removal (by excision or ablation or both, according to surgeons’ preference) versus diagnostic laparoscopy alone. Randomisation with block-stratification will be used. Participants will be given a diagnosis but will not be informed of the procedure they received until 12 months post-randomisation, unless required. Post-operative medical treatment will be according to participants’ preference. Participants will be asked to complete validated pain and quality of life questionnaires at 3, 6 and 12 months after randomisation. Our primary outcome is the pain domain of the Endometriosis Health Profile-30 (EHP-30), via a between randomised group comparison of adjusted means at 12 months. Assuming a standard deviation of 22 points around the pain score, 90% power, 5% significance and 20% missing data, 400 participants are required to be randomised to detect an 8-point pain score difference.

**Discussion:**

This trial aims to provide high quality evidence of the clinical and cost-effectiveness of surgical removal of isolated SPE.

**Trial registration:**

ISRCTN registry ISRCTN27244948. Registered 6 April 2021.

## Administrative information

Note: the numbers in curly brackets in this protocol refer to SPIRIT checklist item numbers. The order of the items has been modified to group similar items (see http://www.equator-network.org/reporting-guidelines/spirit-2013-statement-defining-standard-protocol-items-for-clinical-trials/).

Role of sponsor {5c}	The sponsor is the individual, organisation or partnership that takes on overall responsibility for proportionate, effective arrangements being in place to set up, run and report a research project.

## Introduction

### Background and rationale {6a}

Endometriosis is a chronic oestrogen-dependent, neuro-inflammatory condition that affects approximately 10% of women and those assigned female at birth of reproductive age worldwide [1]. It is characterized by the growth of endometrial-like tissue (‘lesions’) outside of the uterus, most commonly on the peritoneum and ovaries. Symptoms can include chronic pelvic pain, painful periods, painful sex, infertility and fatigue [2]. Endometriosis-associated pain can be disabling and worsen quality of life; the societal economic cost is estimated at £8500 per woman per year globally [3].

Three subtypes of endometriosis have been described: superficial peritoneal endometriosis (SPE), ovarian endometriosis and deep endometriosis [2]. Around 80% of those with endometriosis have SPE. A lack of non-invasive endometriosis tests mean definitive diagnosis is usually achieved by visualisation of the lesions at diagnostic laparoscopy [2]. During laparoscopy, if SPE is found, gynaecologists usually remove it surgically (by excision or ablation) [4, 5]. Investigation and surgical removal require gynaecological surgical expertise and form a significant proportion of the gynaecological workload. However, around 50% of patients who have undergone surgical treatment for endometriosis re-present with persistent, or recurrent, pain within 5 years and surgical reintervention rates are high [6, 7].

Limited evidence exists to support current endometriosis guidelines, showing whether or not surgical removal of isolated SPE improves (or worsens) symptoms and quality of life [4, 5]. A 2014 Cochrane systematic review and meta-analysis of laparoscopic surgery for endometriosis concluded that laparoscopic treatment leads to improved condition-associated pain (cited as ‘better’ or ‘improved’) when compared to diagnostic laparoscopy alone at 6 months (OR 6.58, 95% CI 3.31–13.10) [8]. However, this conclusion is drawn from three randomised controlled trials (RCT), comprising 171 participants with multiple endometriosis subtypes. Furthermore, only one small RCT included in the analysis (69 participants) has follow-up data to 12 months showing benefit of surgery (OR 10.00, 95% CI 3.21–31.17). This led the authors of the systematic review to define the strength of the evidence, based on GRADE criteria, as of moderate and low quality at six and 12 months respectively.

This Cochrane review was updated in 2020, but despite reviewing 1175 articles, the authors reduced the number of included trials examining the effect of laparoscopic treatment of endometriosis on pain to one study of 16 participants with mixed disease type [9]. This was a consequence of altered methodology including application the core outcome set for trial reporting in endometriosis studies [10]. Whilst the authors noted that surgery improved pain at 12 months, the study was considered ‘very low-quality’ evidence. This led the authors to conclude that they were ‘uncertain of the effect of laparoscopic excision on overall pain scores compared to diagnostic laparoscopy only and that further trials are needed’. The paucity of evidence and need for additional studies was further echoed by an additional systematic review and meta-analysis of the effectiveness of laparoscopic surgery for endometriosis, also published in 2020 [11]. Furthermore, the uncertainty surrounding the effectiveness of laparoscopic management of SPE is compounded by the limited evidence to allow an informed selection of specific surgical modalities to remove SPE (ablation versus excision) [12].

Consequently, both the 2017 National Institute of Clinical Excellence (NICE) Endometriosis Guideline and the recent Endometriosis Guideline by the European Society of Human Reproduction and Embryology (ESHRE) recommend further research is needed to determine the effectiveness of laparoscopic removal of isolated SPE to manage endometriosis-associated pain [4, 5]. This call for research was further supported by the outcome of the 2017 James Lind Alliance Endometriosis Priority Setting Partnership that established key research questions most important to those with endometriosis and healthcare practitioners [13].

We, therefore, plan to undertake a multi-centre trial across the UK (called ESPriT2) where women who have only SPE found at diagnostic laparoscopy are randomly allocated to have surgical removal of SPE or diagnostic laparoscopy alone. Surgical removal of SPE in the context of this trial means excision, ablation, or a combination of both. We aim to determine whether surgical removal of endometriotic lesions improves overall endometriosis-associated symptoms and quality of life or whether surgery is of no benefit, exacerbates symptoms or even causes harm.

In this protocol, from now on we use the terms ‘woman’ and ‘women.’ However, it is important to note that endometriosis can affect all people assigned female at birth, all of whom are eligible to participate in this trial.

### Objectives {7}

The primary objective of this trial is to compare laparoscopic removal of isolated SPE versus diagnostic laparoscopy alone in terms of participants’ pain at 12 months post-randomisation.

The secondary objectives of this trial are to compare laparoscopic removal of isolated SPE versus diagnostic laparoscopy alone in terms of:Physical and emotional functioningRequirement for future interventionOccupational outcomesPost-operative pain scoresSurgical complicationsPregnancy eventsCost-effectivenessAdverse events

### Trial design {8}

ESPriT2 is a multi-centre participant-blind parallel-group, superiority randomised (1:1) controlled clinical and cost-effectiveness trial with internal pilot. Figure 1 provides a schematic diagram of the ESPriT2 trial design. The trial design and development of patient facing materials was informed by an ESPriT2 patient and public involvement panel consisting of individuals with lived experience of endometriosis and representatives from patient support organisations.

**Fig. 1 Fig1:**
[figure not shown]
Schematic diagram of ESPriT2 trial design

## Methods: participants, interventions and outcomes

### Study setting {9}

This trial will take place in National Health Service (NHS) hospitals in the UK including both British Society for Gynaecological Endoscopy (BSGE) centres and general gynaecology units. We aim to recruit in up to 70 hospital sites.

### Eligibility criteria {10}

Inclusion and exclusion criteria for trial participants are detailed in Table 1.

**Table 1 Tab1:** Inclusion and exclusion criteria for trial participants

Inclusion criteria	Exclusion criteria
• Women* aged over 16 • Undergoing laparoscopy for the investigation of chronic pelvic pain • In order to be randomised, isolated superficial peritoneal endometriosis (SPE) must be identified at laparoscopy (macroscopically) • Able to give informed consent	• Previous surgical diagnosis of endometriosis • Pregnant • Women* who have undergone hysterectomy and/or bilateral oophorectomy • Women* who are undergoing the following concurrent procedures at the time of laparoscopy o Salpingectomy o Ovarian cystectomy o Oophorectomy o Division of dense adhesions o Endometrial ablation • Ovarian cyst on imaging that is the indication for surgery • Deep endometriosis on imaging or at time of laparoscopy • Endometrioma observed at the time of laparoscopy • Peritoneal ‘pockets’ only noted at laparoscopy

^*^Women includes those assigned female at birth

### Who will take informed consent? {26a}

Potentially eligible participants who are referred or self-refer will be provided with a patient information sheet by a member of the clinical research team at their trial site. Initial contact may be face-to-face during a routine clinic appointment or may be via a telephone/video call via an approved NHS platform by a member of the research team.

Informed consent to participate in the trial will only to be taken by a member of the clinic research team once the patient has had sufficient time to read the patient information sheet, have their questions answered and consider whether they wish to participate in the trial. At least 24 h will be provided for potentially eligible participants to consider participation. All participants who are approached via a call will have the option to attend the hospital to discuss the trial and provide written informed consent in person or provide informed consent verbally over the call. Those who give verbal consent will have the consent form signed by the researcher and a copy of this signed form will be sent to the participant with contact details of the research team should they decide to withdraw consent. At the time of consent, the participant will be reminded that they will be given a diagnosis post-operatively of the findings at the time of laparoscopy but will not be told if surgical removal was carried out. All participants will be asked to re-confirm consent at the time of their laparoscopy and will be asked to wet ink sign the trial consent form before any further research activities are carried out although questionnaires may be completed before this signature is obtained.

### Additional consent provisions for collection and use of participant data and biological specimens {26b}

Participants consented to ESPriT2 will be offered the option to participate in related biomarker (venous blood sample prior to surgery) and imaging (pelvic ultrasound) studies (ESPriT +) for future analysis. In addition, consent will be obtained for longer-term follow-up at two and five years and data linkage for fertility outcomes and surgical reintervention.

## Interventions

### Explanation for the choice of comparators {6b}

Diagnostic laparoscopy is required to diagnose SPE, compared to other endometriosis subtypes (ovarian or deep) that can sometimes be diagnosed using ultrasound by a skilled operator. When SPE is identified, management options include surgical removal (including surgical excision or surgical ablation or both) or no operative treatment. The term surgical removal of SPE in the context of this trial means excision, ablation or a combination of both.

### Intervention description {11a}

At the time of diagnostic laparoscopy, participants will be randomised to diagnostic laparoscopy with surgical removal of SPE or diagnostic laparoscopy alone. For participants allocated to surgical removal of SPE, excision and/or ablation of SPE will be dependent on the operating surgeon’s preference/usual practice. To maintain participant blinding, all participants will have two accessory ports sited in addition to the optical (usually umbilical) port. All participants will be informed of a diagnosis post-operatively but will not be informed whether surgical removal of SPE occurred.

### Criteria for discontinuing or modifying allocated interventions {11b}

Allocation will occur during diagnostic laparoscopy once eligibility (see Table 1) has been confirmed. Perioperative complications or surgical complexity may lead to discontinuation of the allocated intervention, and this is at the discretion of the operating surgeon. Reasons for incomplete removal of disease in those randomised to removal are documented at the end of the procedure if applicable.

### Strategies to improve adherence to interventions {11c}

Not applicable. The trial intervention will occur whilst the patient is anaesthetised.

### Relevant concomitant care permitted or prohibited during the trial {11d}

All participants will be offered routine NHS gynaecological care during the trial, which includes the option of taking any of the current recommended treatment options for endometriosis, such as oral analgesia or hormones (including concurrent levonorgestrel-intrauterine system insertion at surgery). Participants will be permitted to take part in non-interventional studies such as questionnaire studies and bio banking (with the exception of peritoneal biopsies). Participants will be discouraged from co-enrolling in other drug, treatment of pain or surgical trials. If participants co-enrol in another drug, treatment of pain or surgical trial their subsequently collected ESPriT2 data will be excluded from our analysis. Similarly, those enrolled in active intervention phase of another gynaecological trial will be excluded but eligible for inclusion if in long term follow-up phase of other gynaecological trials.

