### Outcomes {12}

The primary outcome in this trial is the ‘pain domain’ of the Endometriosis Health Profile-30 (EHP-30) questionnaire at 12 months post-randomisation.

EHP-30 is a commonly used, condition-specific, patient reported outcome questionnaire that assesses health-related quality of life in endometriosis across five key domains (pain, control and powerlessness, emotional well-being, social support, and self-image) [14]. Evaluation of EHP-30 has shown consistent acceptability, validity, reliability and sensitivity to change suitable for use within endometriosis research and clinical trials of endometriosis interventions [15, 16].

Secondary clinical outcomes will include measures of use of hormones and analgesics, occupational impact, post-operative pain and reproductive outcomes. Secondary outcomes are detailed as follows:Time off work and presenteeism defined by the Work Productivity and Activity Impairment Questionnaire (WPAIQ) at 12 monthsNeed for hormonal medication for endometriosis-related symptoms at 3, 6 and 12 monthsNeed for analgesics for endometriosis-related symptoms at 3, 6 and 12 monthsPain domain of the EHP-30 at 3 and 6 monthsTotal score of EHP-30 at 3, 6 and 12 monthsFatigue symptoms defined by the Brief Pain Inventory (BFI) at 12 monthsNeuropathic pain features identified by PainDETECT™ at 12 monthsUrinary symptoms defined by Pelvic Pain and Urinary Frequency (PUF) Patient Symptom Scale at 12 monthsIrritable bowel symptoms defined by the ROME IV Criteria at 12 monthsPain catastrophizing measured by Pain Catastrophizing Questionnaire (PCQ) at 12 monthsFibromyalgia defined by Fibromyalgia Scale (FS) at 12 monthsSpecific patient reported symptoms defined by Measure Yourself Medical Outcome Profile 2 (MYMOP2)Post-operative (up to 7 days after surgery) pain and analgesic requirements by patient reported diaryLength of hospital stayAdverse events related to surgery at 30 daysSurgical complications at 30 daysSurgical operating timeNeed for further surgery for endometriosis related symptoms at 12 monthsPregnancy events at 3, 6 and 12 months

Outcomes used for the economic evaluation will include:Utility values, derived from EQ-5D-5L health-related quality of life score at 3, 6, and 12 monthsGeneral wellbeing defined by Capability Questionnaire (ICECAP-A) at 3, 6, and 12 monthsCosts and resource use at 3, 6 and 12 months (primary and secondary care use)Impacts on employment, caregiving, and other usual activities (e.g. education)

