### Procedure for unblinding if needed {17b}

At the end of 12 months of post-randomisation follow-up, participants will be given the option to be unblinded. An unblinding facility will be available on the database. If it becomes necessary to unblind a participant prior (e.g. at the participant’s request or for emergency purposes), they will need to contact the local principal investigator (PI) and local research team who will follow the unblinding procedure on the trial database. This will be documented on the database with the reason why the unblinding has taken place as well as the date of the unblinding. Participants unblinded prior to 12 months will still be requested to complete trial outcome measures.

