## Statistical methods

### Statistical methods for primary and secondary outcomes {20a}

Analyses will primarily be intention-to-treat where all randomised participants will be included in the analysis retained in the group to which they were allocated and for whom outcome data are available. All results will be presented as point estimates, 95% confidence intervals with associated *p*-values. We will specify all analyses to be undertaken in a statistical analysis plan to be finalised before database lock.

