### Primary outcome analysis

The primary outcome, pain domain of the EHP-30 at 12 months, will be compared using a linear regression model to estimate the mean difference in outcome, including fixed effect terms for surgical removal group, baseline pain score and stratification variables. Unadjusted results will also be presented to support the findings of the primary analysis. Secondary analyses will include using repeated-measures (multi-level) models incorporating outcome data from other follow-up time points.

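### Excluding data collected after co-enrolment in another trial contradicts the stated intention-to-treat analysis and can bias the primary comparison

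*Protocol article*

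**What the plan says.** Section {11d} of the protocol article discourages participants from joining other drug, pain-treatment or surgical trials, and then sets an analysis rule for those who do: "If participants co-enrol in another drug, treatment of pain or surgical trial their subsequently collected ESPriT2 data will be excluded from our analysis".

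Section {20a} defines the main analysis set: "Analyses will primarily be intention-to-treat where all randomised participants will be included in the analysis", kept in their allocated group, with the qualifier "for whom outcome data are available".

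The Outcomes section {12} fixes the endpoint: "The primary outcome in this trial is the ‘pain domain’ of the Endometriosis Health Profile-30 (EHP-30) questionnaire at 12 months post-randomisation". The primary model is a linear regression "including fixed effect terms for surgical removal group, baseline pain score and stratification variables", with repeated-measures models as secondary analyses. Under {20c}, imputation of missing values is a sensitivity analysis that will be considered only if enough values are missing.

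Other treatment after randomisation does not lead to exclusion. Section {11d} allows participants "the option of taking any of the current recommended treatment options for endometriosis, such as oral analgesia or hormones" and attaches no such rule to it.

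**The concern.** The two sections give different answers to a basic question: who is in the primary analysis? A participant who completes the 12-month questionnaire after joining another trial is in under {20a} and out under {11d}.

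The answer matters because joining another trial is not a chance event. It follows randomisation, and persisting pain is a plausible reason for it. Persisting pain is also what the primary outcome measures. If removal changes pain, in either direction, co-enrolment may differ between the arms. The participants left in each arm are then no longer the groups that randomisation formed. Because the rule discards observed values, the bias it risks is avoidable.

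**Working it through.** **1. Can the two sections be read together?** The only candidate is the availability qualifier in {20a}. It does not help: the rule in {11d} applies to data that have been collected, and these are available. Nor does {11d} limit the exclusion to a secondary analysis. The primary endpoint is at 12 months, so co-enrolment at any time before that visit removes it. Baseline scores, and any 3- or 6-month scores obtained before co-enrolment, are kept.

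**2. The plan's own figures.** Inputs from the Sample size section {14}: difference 8, SD 22, two-sided 5%, 90% power, 20% loss.

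- n per arm = 2 × (1.960 + 1.282)² × 22² / 8² = 158.9, so 159 by the normal approximation. The t-based calculation gives the stated 160.
- 160 / (1 − 0.20) = 200 per arm, 400 in total.

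The stated size reproduces, and this point does not change it. If co-enrolment exclusions fall within the 20% allowance, no power is lost against plan. If they come on top of it, 2% leaves 156 per arm (89.5% power), 5% leaves 150 (88.3%) and 10% leaves 140 (about 86%).

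**3. Shift in the primary contrast.** Take higher scores as more pain. In one arm let p be the proportion excluded and D the gap between the mean of excluded and of retained participants.

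- Full-arm mean = (1 − p) × retained mean + p × (retained mean + D) = retained mean + p × D.
- Exclusion therefore lowers that arm's mean by p × D.
- With the same D in both arms, the control-minus-removal difference falls by (pC − pR) × D.

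The document gives neither p nor D. All values below are assumptions.

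| Excluded, control v removal | D (points) | Shift (points) | Share of 8 |
|---|---|---|---|
| 5% v 5% | any | 0 | 0% |
| 1% v 0.5% | 15 | 0.005 × 15 = 0.075 | 1% |
| 5% v 2% | 10 | 0.03 × 10 = 0.3 | 4% |
| 10% v 5% | 15 | 0.05 × 15 = 0.75 | 9% |
| 15% v 5% | 20 | 0.10 × 20 = 2.0 | 25% |
| 10% v 5% | −10 | 0.05 × (−10) = −0.5 | −6% |

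A positive shift shrinks a true benefit of removal. The last row shows the reverse: co-enrollers score better at 12 months than the rest of their arm, and leaving them out enlarges the contrast. The calculation uses unadjusted means. Adjustment for baseline pain would reduce the shift so far as baseline explains the gap.

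**The case against.** The strongest reply is that the event is probably rare and the harm reversible. Co-enrolment is discouraged. Participants are blinded, so knowledge of allocation should not drive it, although pain still can. The data are collected and only left out of analysis, and the SAP is to be finalised before database lock. All of this stands, and it lowers the severity. It does not remove the contradiction: a SAP that follows one section breaches the other.

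The sponsor may also wish to keep another trial's treatment from contaminating the result. That is a fair supplementary question. It does not justify excluding participants from the main analysis on a post-randomisation event that may depend on pain.

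A reader might infer three stronger claims, which the document does not support:

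- **That the bias always runs towards the null.** This requires co-enrollers still to be worse at 12 months, and to be more numerous in the arm with more pain. They may improve on the other trial's treatment, and equal rates with equal gaps give no bias.
- **That imputation under missing-at-random cannot repair it.** Baseline and earlier follow-up scores are kept and partly measure the pain that would lead someone to co-enrol. Such methods might reduce or remove the bias. The document does not settle this, and {20c} makes imputation only conditional.
- **That the rule also conflicts with section {17b}.** There, "Participants unblinded prior to 12 months will still be requested to complete trial outcome measures". That concerns early unblinding, a different event, and data collection rather than analysis. It is a contrast in approach, not a contradiction.

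**Conclusion.** The conflict between {11d} and {20a} is established from the text alone and needs no outside figure. That the exclusion can bias the primary comparison follows from its timing and its plausible link to pain. That it will do so, by how much and in which direction, cannot be determined from the document.

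The illustrative 0.3 to 2.0 points rests on assumed exclusion rates and on an assumed gap of 10 to 20 points against retained participants in the same arm. At lower rates the shift is negligible. This should be fixed, because the passage decides who enters the primary analysis, but it does not undermine the design or the sample size. The sentence in {11d} about participants in the active phase of another gynaecological trial reads as an entry restriction and is not part of this point.

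**What to change.** Replace the exclusion sentence in {11d} with wording such as: *Participants who co-enrol in another trial remain in follow-up, and all their collected data are included in the primary intention-to-treat analysis in the group to which they were allocated. The date of co-enrolment and the type of trial are recorded.* If the effect of another trial's treatment is of interest, add to the SAP one sensitivity analysis that leaves out data collected after co-enrolment. The discouragement of co-enrolment can stay as it is.

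The cost is one sentence in the protocol, a matching line in the SAP, and a small extra data item, since the forms described in the article do not list co-enrolment. The sample size is unchanged. At manuscript submission 89 of the planned 400 had been randomised, and the SAP only has to be final before database lock, so on the article's own timeline the change could be made in time.
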